#### Power calculation

Power calculation is based on the primary outcome: Primary care interval. The sample size is calculated to detect a reduction in the longest primary care intervals >20 days [56] from 25% to 20%. The expected effect is reduced according to an intervention to intervene analysis; we expect a GP participation rate at the CME-meetings of 40%. Uncorrected for clustering and repeated measures, a total sample size (N) of 5116 patients would be required (power of 99% and significance level of 0.05).

To accommodate the stepped wedge clustering effect N has to be multiplied by the design effect (DE) [57]: N_*sw*_ = DE*N, where$$ DE=\frac{1+\rho \left(ktn+bn-1\right)}{1+\rho \left(\frac{1}{2}ktn+bn-1\right)}\cdotp \frac{3\left(1-\rho \right)}{2t\left(k-\frac{1}{k}\right)} $$

Here, *ρ* is the intra-cluster correlation, *k* is the number of steps, *n* is the average cluster size, *b* is the number of baseline measurements and *t* is the number of measurements after each step. In our study *k* = 8, *b* = *t* = 1. Furthermore, we assume that *ρ* = 0.05, as it is a typical value for intra-cluster correlation for clinical outcomes in primary care [58]. The cluster size can be expressed as *n* = *N*_sw_ / *c*, where *c* is the number of clusters. The number of clusters is known in advance (*c* = 8) and the question is how many subjects per cluster should be sampled to provide the power required. Using the equations described above, this cluster size is estimated as *n* = 200 through an iterative procedure. Therefore, the total sample required (*N*_sw_) is 1,653. In Central Denmark Region, 5,400 new cancer patients are expected in an 8-month period. We assumed that 40% [59] of those (2,200) will be referred from general practice to a cancer fast-track pathway. With an assumed PPV for diagnosing cancer in fast-track pathway on 20% and an assumed GP response rate on 70%, we expect to receive one-page forms with information on primary care intervals on 7,700 patients. Thus, it is considered that the study has ample strength—also in relation to three stratified subgroups of GPs and adjustment for multiple predictors.

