### Statistical analyses

For the descriptive part, differences will be tested using appropriate parametric and nonparametric statistics. The effect of the intervention will be analysed in a generalised, linear, random-effects model with random effect of GPs. The data will be used to assess whether further modelling of inter-correlation within practice and within clusters is required, and whether the intervention effects are equal for all GPs or in random interaction with them. Analyses will be performed both in the full GP population “intention to intervene” (cluster level) and in the three GP subgroups: 1) GPs who participated in the CME, 2) GPs who did not participate in the CME, but had at least one colleague who participated, and 3) GPs who did not participate in the CME and who had no colleagues who participated. A colleague is defined as a GP with the same clinic address as the respondent. The intervention effect on GP knowledge and attitude will be measured in a before-after analysis.

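### The power calculation does not say whether the 5-point effect is before or after the reduction for 40% attendance, and on neither reading do 7,700 forms deliver the stated 99% power

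*Protocol article*

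**What the plan says.** All of this is in the Protocol article, under Power calculation unless noted.

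- Target: "The sample size is calculated to detect a reduction in the longest primary care intervals >20 days [56] from 25% to 20" per cent.
- Allowance for non-attendance, in the next sentence: "The expected effect is reduced according to an intervention to intervene analysis; we expect a GP participation rate at the CME-meetings of 40" per cent.
- Size before the design effect: "a total sample size (N) of 5116 patients would be required (power of 99% and significance level of 0.05").
- Stepped-wedge inputs: "In our study *k* = 8, *b* = *t* = 1"; rho is 0.05 because "it is a typical value for intra-cluster correlation for clinical outcomes in primary care"; "The number of clusters is known in advance (*c* = 8"), with cluster size defined as the stepped-wedge total divided by the number of clusters.
- Result: "Therefore, the total sample required (*N*_sw_) is 1,653", with about 200 patients per cluster.
- Expected yield: 7,700 one-page forms. The section concludes that the study is amply powered, also for the three GP subgroups and for adjustment for several predictors.
- Statistical analyses: "Analyses will be performed both in the full GP population" (intention to intervene) and in three subgroups defined by own and colleagues' attendance. Neither is labelled primary.

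**The concern.** A reduction for 40% attendance should link two effects: one in GPs who attend and a smaller one in all GPs invited. The section prints only one pair of rates, so a reader cannot tell which of the two the 99% refers to. The choice matters because 5 points in attenders could be as little as 2 points in the full population, while 5 points in the full population could require 12.5 points in attenders.

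The step from 5,116 to 1,653 raises a second question: whether the design effect was applied to the quantity it is defined for. Together the two points decide whether the claim of ample power can be relied on. If it cannot, a null full-population result might be read as evidence of no effect when a small but real effect would usually have been missed.

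**Working it through.** **1. The plan's N.** Inputs: 25% and 20%, alpha 0.05, power 99%. Two-sided testing and 1:1 allocation are assumed; they reproduce the stated figure.

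n per arm = [1.960·√(2p̄(1−p̄)) + 2.326·√(p₁(1−p₁)+p₂(1−p₂))]² / (p₁−p₂)², with p̄ = 0.225

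= [1.960·√0.34875 + 2.326·√0.3475]² / 0.05² = 2,558, so N = 2 × 2,558 = **5,116**, as stated.

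The 40% therefore enters only if it is already inside the 5 points.

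**2. Reading A: 5 points is the effect in attenders.** Assume that non-attenders do not change and that attenders account for 40% of patients. The full-population effect is 0.4 × 5 = 2 points, 25% versus 23%.

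- N for 99% power, same formula with p̄ = 0.24: [1.960·√0.3648 + 2.326·√0.3646]² / 0.02² = 16,751 per arm, or **33,502** in total before any design effect (14,314 for 80%).
- Power at 5,116: Φ((0.02 − 1.960 × 0.01194)/0.01194) = Φ(−0.285) = **about 39%**.
- With spill-over to colleagues the contrast lies between 2 and 5 points. At 3 points (25% versus 22%), power at 5,116 is about 72%.

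**3. Reading B: 20% is already the diluted target.** 5,116 at 99% is then arithmetically right. With no change in non-attenders, the effect in attenders is 5/0.4 = 12.5 points, 25% to 12.5%.

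**4. The plan's stepped-wedge total.** With k = 8, b = t = 1, rho = 0.05 and n = total/8, iteration settles at n = 206.6:

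DE = [1 + 0.05(9 × 206.6 − 1)] / [1 + 0.05(5 × 206.6 − 1)] × 3(0.95)/(2 × 7.875) = 0.3231

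0.3231 × 5,116 = **1,653**, as stated.

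**5. What n means in that formula.** The term ktn + bn is the number of observations in one cluster over the whole study, here 8n + n = 9n. So n is per cluster per measurement. The plan instead sets n to the cluster's total. With n = 206.6 per measurement, the study needs 8 × 9 × 206.6 = about 14,877 observations, nine times 1,653.

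**6. Direct check.** Linear mixed model with a random cluster effect and fixed period effects, 8 clusters × 9 periods, rho 0.05, one cluster crossing over per step, normal approximation. At 14,877 observations it gives 99% power for 25% versus 20%, which confirms the per-measurement reading. With 7,700 forms there are 7,700/72 = 107 per cell, and the standard error of the effect is about 0.0165 (0.0162 for the 5-point contrast):

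| Full-population effect | Power at N = 5,116, no clustering | Power with 7,700 forms, mixed model |
|---|---|---|
| 5 points (25% vs 20%) | 99% | 87% |
| 3 points (25% vs 22%) | 72% | 45% |
| 2 points (25% vs 23%) | 39% | 23% |

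The difference detectable with 80% power is (1.960 + 0.842) × 0.0165 = **about 4.6 points**, or 4.6/0.4 = 11.5 points in attenders if nobody else changes. At the plan's own 1,653 patients, the same model gives about 31% power for 5 points.

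**The case against.** The strongest reply is that the second sentence explains the first: 25% to 20% is the target after the reduction. On that view there is no arithmetic error. The match of 5,116 with 25% versus 20% cannot settle the matter, because both readings predict it. This stands, and it is why the point is not that the 5,116 is wrong.

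A reader might infer that power for the full-population analysis is simply 23% rather than 99%. The documents do not support that as a flat statement. Dilution alone takes 99% to about 39% at 5,116. The 23% needs three conditions together: reading A, no effect at all outside attenders, and the mixed model at 7,700 forms in place of the plan's use of its design effect. That use (n = 7,700/8) would give an effective size of 23,682 and 95% power for 2 points. The 95% is not a defence, because it rests on the reading of n shown above to be inconsistent with the formula.

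The no-spill-over condition is also a worst case. Strengths and limitations expects much of the effect to arise through GPs working together, and Setting gives 836 GPs in 417 clinics, about two per clinic. Two points is therefore a lower bound under reading A.

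Finally, a reader might take the full-population analysis to be the declared primary one. Statistical analyses does not label it so. The power section, however, ties its sizing to that analysis, and that is enough for the point.

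**Conclusion.** The point holds in two parts. First, the section is ambiguous: 5,116 is the size for a 5-point difference, and nothing shows whether the 40% attendance has been taken into account. On one reading, power at that N is between about 39% (no spill-over) and 99% (full spill-over). On the other, the calculation is right but rests on an unstated halving of long intervals among attenders.

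Second, and on either reading, the design effect is applied to the wrong n. The expected 7,700 forms give about 87% power for a 5-point full-population effect, not 99%, and 23% to 45% for 2 to 3 points. The conclusion of ample power, which extends to subgroups and multiple adjustment, is not supported by the plan's own inputs.

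These figures assume two-sided testing, rho 0.05 for the eight geographical clusters as the plan uses it, equal numbers per cluster and period, and attenders contributing 40% of patients. They concern the stated power only; no estimate or data collection is affected.

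**What to change.** In Power calculation:

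1. State the effect expected in attenders and the diluted full-population effect as two separate pairs of rates. Say which pair produced 5,116, and state the spill-over assumed for non-attending colleagues. If 20% is the diluted target, give and justify the attender effect it implies (12.5% with no spill-over).
2. Apply the design effect with n per cluster per measurement, or use the mixed-model variance directly, and correct the 1,653.
3. Replace the 99% figure and the claim of ample power with the power for the 7,700 expected forms over the plausible range (about 23% at 2 points, 45% at 3, 87% at 5) and the detectable difference of about 4.6 points at 80%.

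The cost is rewording and a less favourable stated figure. Trial status reports that the meetings are over and the forms collected, but that data cleaning and register extraction have not begun, so the correction can be made before analysis with no change to data collection.

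### The required 1,653 patients is a per-occasion count read as the trial total; the plan's own formula needs about 14,900 forms for 99% power, and the 7,700 expected give about 87%

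*Protocol article*

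**What the plan says.** The Power calculation section takes the primary care interval as its basis: "The sample size is calculated to detect a reduction in the longest primary care intervals >20 days [56] from 25% to 20" per cent, with "power of 99% and significance level of 0.05". Before any allowance for clustering, "a total sample size (N) of 5116 patients would be required". That number is multiplied by a stepped-wedge design effect, for which "In our study *k* = 8, *b* = *t* = 1" and "we assume that *ρ* = 0.05". The plan calls n the average cluster size, sets it to the total divided by the eight clusters, iterates to n = 200, and concludes: "Therefore, the total sample required (*N*_sw_) is 1,653".

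It then estimates the yield of the 8-month collection period: "we expect to receive one-page forms with information on primary care intervals on 7,700 patients". From the comparison of the two totals it draws its assurance: "Thus, it is considered that the study has ample strength—also in relation to three stratified subgroups of GPs and adjustment for multiple predictors".

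The Data section and its subsection on the one-page forms describe one form for each referred patient, holding one referral date and one date of first presentation.

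**The concern.** The final figure is about a third of the number needed with no clustering at all (1,653 / 5,116 = 0.32). With one outcome per patient, correlation within clusters, and calendar time to control for, a stepped wedge should not need a third of the patients of an individually randomised trial. Individual randomisation of 1,653 patients would itself give only 68% power for this difference.

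If 1,653 is not the trial total, three statements lose their basis: the 99% power, the margin of 7,700 over 1,653, and the assurance that this margin covers three subgroups and adjustment for several predictors.

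**Working it through.** **Inputs (Power calculation section).** Proportions 25% and 20%; alpha 0.05 (two-sided reproduces the plan's N); power 99%; k = 8; b = t = 1; ρ = 0.05; c = 8 clusters; 7,700 forms expected (2,200 / 0.20 × 0.70 = 7,700).

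**1. Reproduce 5,116.** Two proportions, pooled variance under the null, no continuity correction:

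n per arm = [1.960 × √(2 × 0.225 × 0.775) + 2.326 × √(0.25 × 0.75 + 0.20 × 0.80)]² / 0.05² = 2,558, so N = 5,116.

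**2. Reproduce 1,653.** Iterate n = DE × 5,116 / 8 with the printed formula. It settles at n = 206.6 (the plan rounds to 200):

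DE = [1 + 0.05 × (9 × 206.6 − 1)] / [1 + 0.05 × (5 × 206.6 − 1)] × 3 × 0.95 / [2 × (8 − 1/8)] = 1.786 × 0.1810 = 0.3231

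0.3231 × 5,116 = 1,653. The arithmetic is right.

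**3. What n counts.** The numerator has the familiar form 1 + ρ × (observations per cluster − 1), with ktn + bn as the number of observations. At k = 8 and b = t = 1 that is 9n. So n is the number observed in a cluster at each of nine occasions, and 8n = 1,653 is the number per occasion across all clusters. It would be the number of people in the trial only if the same people were measured nine times. Here each patient is measured once.

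**4. Trial total.** c × (b + kt) × n = 8 × 9 × 206.6 = 14,877. Other values of ρ in the same formula give about 15,030 at 0.01, 14,150 at 0.10 and 8,770 at 0. All exceed 7,700.

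**5. Power of 7,700 forms from the plan's own formula.** n = 7,700 / 72 = 106.9, DE = 0.3207, equivalent individually randomised N = (7,700 / 9) / 0.3207 = 2,667, power 87%.

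**6. Check without the design-effect formula.** Generalised least squares on 8 clusters by 9 equal periods, with fixed period effects, a random cluster effect, total variance 0.225 × 0.775 and ICC 0.05. Power = Φ(0.05 / SE − 1.96).

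| Total forms | SE (percentage points) | Power |
|---|---|---|
| 1,653 | 3.40 | 31% |
| 7,700 | 1.62 | 87% |
| 14,877 | 1.17 | 99.0% |

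That 14,877 returns the 99% target confirms the nine-fold reading. In the same model, 80% power needs about 6,300 forms and 90% about 8,470.

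**7. Sensitivity at 7,700 forms.**

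| Assumption | Power |
|---|---|
| ICC 0.01 to 0.10 at cluster level | 87% to 89% |
| Cluster-level ICC 0.001 | 94% |
| ICC 0.05 at practice level only (417 practices) | 95% |
| About twelve 3-week periods, to fill 8 months | 83% |
| Within-cluster correlation between periods 0.9 of that within a period | 70% |

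The document supplies neither the period lengths nor the 0.9; both are assumptions.

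**8. Subgroups.** Assume that GPs who attend (40%) supply 40% of the forms: 0.4 × 7,700 = 3,080. The same model gives SE 2.53 points. Power is 51% for a 5-point effect. If 5 points is the effect averaged over all GPs and only attenders respond, their effect is 5 / 0.4 = 12.5 points and power is above 99%.

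**The case against.** The strongest reply is that the trial is not in trouble. About 87% exceeds the conventional 80%, and the shortfall is against an unusually demanding 99%. The Trial status section says the forms were already collected, so no recruitment decision depends on this. That stands. A reader might infer from 7,700 against 14,900 that the main comparison is seriously underpowered; the figures do not support that.

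A second reply is that the result depends on where the correlation lies. The plan describes 0.05 as typical of primary care, and the Statistical analyses section starts from a random effect of GPs, adding practice and cluster correlation if the data require it. With the correlation mainly at practice level, power is about 95%. This also stands, and it means that 14,900 is the requirement under the plan's own formula rather than under every model. It does not restore 1,653 as a total, nor 99% power at 7,700 forms under the plan's assumptions.

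A third reply concerns subgroups. A reader might infer that all three are low-powered. The document does not establish that. It says that the expected effect has been reduced for 40% participation, which suggests that 25% to 20% is already diluted and that attenders should show more. The wording is not conclusive, because 5,116 is simply the N for 25% against 20%. GPs with neither attendance nor an attending colleague would be expected to show little effect anyway. What can be said is that the assurance for subgroups rests on a surplus that does not exist.

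Finally, a reader might take n as the number per 3-week period. The Study design section fixes three weeks between clusters, but baseline and final periods are not given, and nine 3-week periods (27 weeks) do not fill eight months. Per measurement occasion is as far as the text goes.

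**Conclusion.** The stated total is wrong by a factor of nine. Under the plan's formula, its ICC of 0.05 and one form per patient, 99% power for 25% against 20% needs about 14,900 forms. The expected 7,700 are 0.52 of that, not 4.7 times the requirement. They give about 87% power: 94% to 95% if clustering is mainly at practice level or the geographic ICC is near 0.001, and about 70% under the assumed 0.9 between-period correlation. The 99% power and the surplus are not delivered, but the overall comparison keeps acceptable power. The claim of ample strength for subgroups is unsupported; whether a given subgroup is well or poorly powered cannot be settled until the plan states the effect and share of forms it assumes there.

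**What to change.** In the Power calculation section:

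- Define n as patients per cluster per measurement occasion, and give the total as c(b + kt)n, about 14,900 for 99% power.
- Report the power that 7,700 forms give (about 87% under the plan's formula), with a short range over correlation structures, marking as assumptions those the plan does not specify.
- Remove the ample-strength statement, which rests on 1,653.
- State whether 25% to 20% is the effect after dilution for 40% participation. For each of the three GP subgroups, give power or expected confidence-interval width under its own assumed effect and share of forms.

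The cost is a rewritten paragraph and a short calculation. No more patients are needed, and no outcome or analysis model changes. The downside is that the stated power becomes less favourable.

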### Ethical approval

The Danish Research Ethics Committee (j.no. 10/2014) concluded that no approval is necessary. The study was approved by the Danish Data Protection Agency (j.no. 2009-41-3471). The Danish National Board of Health gave legal permission to obtain information from the GPs’ medical records without permission from the patients (j.no. 3-3013-149/1/HKR). The regional Data Protection Agency gave permission to use the regional database (PAS) and the radiological database to obtain information on patients investigated in a cancer fast-track pathway (j.no. 1-16-02-262-12). The study is registered as NCT02069470 on ClinicalTrials.gov.

### Trial status

The study is ongoing. The CME meetings were conducted in the period September 2012 to May 2013. We have not yet conducted data cleaning or obtained data from registers; only the data from forms and questionnaires have been collected. Furthermore, we have not yet developed the algorithm to identify referred patients from the Primary Care Referral Registry.

## Discussion

We developed a multifaceted CME in early cancer diagnosis targeting the individual GPs using a step-wise approach for the development of complex interventions [34]. We identified key elements and analysed them by using the COM-B system described by Michie et al. [46]. The effect evaluation will be conducted in a geographical cluster randomised stepped wedge study. The effect of the CME will be measured at three levels: GP knowledge and attitude, GP activity and patient outcomes.

### Strengths and limitations of the study

With a detailed description of the CME elements, training process and context, we have tried to optimise the possibilities for an adaptation/replication in other settings.

The time frame of the present study did not afford us with the possibility to conduct an explorative study on the target group before the trial; instead, a full-scale CME was conducted in an external regional cancer steering group, and the findings were subsequently evaluated, discussed and approved.

Randomising individual GPs to the CME intervention was considered unfeasible as much of the effect would include GPs working together and discussing cancer diagnosis within practices and in the CME groups. Preventing GPs from participation was considered unethical since the CME was a part of the Danish Cancer Plan, and it was considered important that all patients could benefit from an improved clinical practice. A cluster randomised stepped wedge study was thus preferred. Using this design, we will be able to control for time trends by allowing contemporaneous comparisons across clusters at different time periods.

Designing a study in real life, however, raised some challenges with regard to controlling the intervention. A specific CME date was offered to all GPs, but they were free to decide whether they wanted to participate or not. The collected data will allow us to compare the three GP subgroups of each cluster at a baseline level to explore potential selection bias.

GP knowledge, attitude and self-assessed readiness to refer will be measured by online questionnaires before and after the CME to allow paired analyses to be performed. The GPs were informed in the invitation letter that the questionnaire attempted to measure activity related to cancer diagnosis in general practice. This could have influenced the responses.

By placing a pad with forms in each GP office and by sending regular reminders (every second week), we expect to collect prospective data, i.e. to obtain data before the GPs know whether the referred patient had cancer or not. In cases where the GP forgot to complete a form and had to be requested to do so, information bias can occur. Furthermore, lead time bias will be considered when reporting the 1-year survival. This outcome will be evaluated in close relation to potential change in cancer stage.

